# Effect of early sleep apnoea treatment with adaptive servo-ventilation in acute stroke patients on cerebral lesion evolution and neurological outcomes: study protocol for a multicentre, randomized controlled, rater-blinded, clinical trial (eSATIS: early Sleep Apnoea Treatment in Stroke)

**DOI:** 10.1186/s13063-020-04977-w

**Published:** 2021-01-22

**Keywords:** Sleep-disordered breathing, Stroke, MRI evolution, Treatment, Adaptive servo-ventilation, Randomized controlled trial, Outcome

## Abstract

**Background:**

Sleep-disordered breathing (SDB) is highly prevalent in acute ischaemic stroke and is associated with worse functional outcome and increased risk of recurrence. Recent meta-analyses suggest the possibility of beneficial effects of nocturnal ventilatory treatments (continuous positive airway pressure (CPAP) or adaptive servo-ventilation (ASV)) in stroke patients with SDB. The evidence for a favourable effect of early SDB treatment in acute stroke patients remains, however, uncertain.

**Methods:**

eSATIS is an open-label, multicentre (6 centres in 4 countries), interventional, randomized controlled trial in patients with acute ischaemic stroke and significant SDB. Primary outcome of the study is the impact of immediate SDB treatment with non-invasive ASV on infarct progression measured with magnetic resonance imaging in the first 3 months after stroke. Secondary outcomes are the effects of immediate SDB treatment vs non-treatment on clinical outcome (independence in daily functioning, new cardio-/cerebrovascular events including death, cognition) and physiological parameters (blood pressure, endothelial functioning/arterial stiffness). After respiratory polygraphy in the first night after stroke, patients are classified as having significant SDB (apnoea-hypopnoea index (AHI) > 20/h) or no SDB (AHI < 5/h). Patients with significant SDB are randomized to treatment (ASV+ group) or no treatment (ASV− group) from the second night after stroke. In all patients, clinical, physiological and magnetic resonance imaging studies are performed between day 1 (visit 1) and days 4–7 (visit 4) and repeated at day 90 ± 7 (visit 6) after stroke.

**Discussion:**

The trial will give information on the feasibility and efficacy of ASV treatment in patients with acute stroke and SDB and allows assessing the impact of SDB on stroke outcome. Diagnosing and treating SDB during the acute phase of stroke is not yet current medical practice. Evidence in favour of ASV treatment from a randomized multicentre trial may lead to a change in stroke care and to improved outcomes.

**Trial registration:**

ClinicalTrials.gov NCT02554487, retrospectively registered on 16 September 2015 (actual study start date, 13 August 2015), and www.kofam.ch (SNCTP000001521).

**Supplementary Information:**

The online version contains supplementary material available at 10.1186/s13063-020-04977-w.

## Background

Sleep-disordered breathing (SDB) is a highly prevalent comorbidity in acute ischaemic stroke patients [1, 2]. About two-thirds of this patient group suffers from any degree of SDB, up to 40% present an apnoea-hypopnea index (AHI) above 20/h and one third even suffers from a severe form with an AHI > 30/h [1–4].

A bidirectional relationship between SDB and stroke can be assumed [5, 6]. SDB, especially the obstructive subtype, is not only an independent risk factor for stroke (e.g., [7]) but is also associated with a more rapid progression of stroke severity, with higher blood pressure levels and longer hospitalization in the acute phase [8–10]. Chronically, stroke patients with comorbid SDB exhibit worse functional outcome and higher mortality [11, 12]. Several pathophysiological conditions associated with SDB are believed to cause harmful effects [13]. These include intermittent hypoxemia, intrathoracic pressure changes and sympathetic activation, which may trigger cardiac arrhythmias or blood pressure swings [14, 15], potentially leading to harmful hypo- or hyper-perfusion of acutely damaged brain tissue. The ischaemic penumbra may be amenable to reperfusion. Consequently, any treatment stabilizing cerebral perfusion and preserving constant brain tissue oxygenation may be helpful [16].

Effective methods to normalize obstructive SDB are available, including continuous positive airway pressure (CPAP). However, central SDB is also often present in acute stroke. Some studies even suggest that new-onset SDB is often of central type [17, 18]. In particular, central apnoeas and central periodic breathing were also reported in patients with unilateral lesions of variable topography without a disturbed level of consciousness or overt heart failure, which potentially involve autonomic or volitional brain areas participating in respiratory control [19]. Adaptive servo-ventilation (ASV) is considered superior to CPAP in correcting both central and obstructive SDB [20]. Meta-analyses on the initiation of SDB treatment in the very first days following stroke postulate a positive association with neurofunctional improvement with CPAP but with a considerable heterogeneity across the included trials [21]. Prior studies reporting a positive impact of CPAP treatment after acute stroke mainly included TIA patients, milder strokes and younger patients. More recently, Bravata and colleagues found better neurological functioning at about 1 year post stroke, assessed with the modified Rankin scale (mRS) and the National Institute of Health Stroke Scale (NIHSS), in ischaemic stroke patients with obstructive sleep apnoea (OSA) and compliant CPAP use but not in the intention-to-treat analysis [22]. In this study, CPAP was initiated with a median time delay of about 2 months from onset of stroke symptoms. These studies have not assessed the acute neuroradiological evolution or change in network connectivity in the acute stroke phase under ASV treatment versus no treatment.

Thus, eSATIS aims to investigate the effects of immediate treatment of significant SDB (AHI > 20/h) with non-invasive ASV started within 48 to 68 h after stroke onset on the ischaemic lesion evolution assessed by magnetic resonance imaging (MRI) 3 months after the event. The secondary trial objectives assess whether immediate onset of ASV treatment in stroke patients with SDB improves clinical stroke outcomes and physiological parameters. The overall impact of significant SDB compared to no SDB on theses outcomes is also assessed.

## Methods

### Study design and setting

The present study is a prospective, multicentre, randomized, open-label, rater-blinded clinical trial in ischaemic stroke patients with SDB (AHI > 20/h, approximate recruitment goal *n* = 134), including a control cohort of stroke patients without SDB observed for the same duration of time (no SDB; AHI < 5/h, approximate recruitment goal *n* = 66). The study is conducted at 6 study sites in 4 countries: Bern University Hospital (Switzerland), Cantonal Hospital St. Gallen (Switzerland), Almazov National Medical Research Centre St. Petersburg (Russia), Grenoble Alpes University Hospital (France), Medical Centre of the Johannes Gutenberg University Mainz (Germany) and Charité - Universitätsmedizin Berlin (Germany). It was designed and initiated by an interdisciplinary research team of neurologists, neuroradiologists and pulmonary physicians at the Bern University Hospital and is coordinated by this centre.

The trial was registered on ClinicalTrials.gov (NCT02554487) on 16 September 2015 1 month after recruitment of the first patient (first patient in 13 August 2015) as well as on www.kofam.ch (SNCTP000001521). The initially monocentric trial became multicentre in May 2017 as the second centre in Switzerland, St. Gallen, was initiated and was then successively extended to Mainz, Berlin, St. Petersburg and Grenoble. Feasibility of the trial at each centre was evaluated based on the number of admitted stroke patients to a centre, availability of required infrastructure and qualified staff in the necessary disciplines to conduct the trial: neurology, pulmonary medicine and/or sleep medicine as well as neuroradiology. Feasibility of diagnosing and treating SDB in acute stroke patients was shown in former clinical studies of the Bernese study team (SAS CARE 1 & 2, [23–25]).

Screening and recruitment procedures for the current trial (described in the following paragraph) were established and evaluated within clinical routine at the coordinating centre in Bern.

### Screening and recruitment of participants

We recruit patients suffering from an ischaemic stroke in the acute phase of stroke (hospitalization within 24 h of symptom onset). Potential participants are identified at admission to the emergency and stroke units of the 6 participating study sites following review of patients’ electronic medical records. Screening and recruitment requires the presence of a study physician, the non-invasive ventilation and MRI team and is usually performed from Sunday night until Friday morning. Inclusion and exclusion criteria are outlined in Table 1 and are checked according to a two-step screening algorithm provided to all centres by the coordinating centre of Bern.

**Table 1 Tab1:** Participant inclusion and exclusion criteria and criteria for randomization

*Inclusion criteria*	*Exclusion criteria*
1. Informed consent as documented by signature 2. Admission to one of the participating centres 3. Age 18–85 years 4. Ischaemic stroke detectable by neuroimaging, affecting internal carotid artery, anterior cerebral artery (ACA), middle cerebral artery (MCA), posterior cerebral artery (PCA) and/or branches thereof 5. Symptom onset to admission < 24 h 6. AHI > 20/h or < 5/h	1. Primary haemorrhagic stroke or secondary parenchymal haemorrhage (PH 1 and PH 2 according to ECASS) 2. Small strokes (diameter < 1.5 cm) 3. Coma/Stupor 4. Clinically unstable or life-threatening condition 5. Heart failure defined as congestive heart failure (CHF) functional class NYHA III-IV **OR** CHF NYHA II **and** hospitalization caused by CHF in the preceding 24 months **OR** left ventricular ejection fraction ≤ 45% 6. Intubation or oxygen supply > 2 L/min. 7. Known progressive neurological diseases 8. Drug or alcohol abuse 9. Inability to follow study procedure 10. Pregnancy 11. Any given contraindications to MRI or MRI-contrast agent 12. Any given contraindications to ASV treatment 13. Protocol addendum made on 28.05.2020: Exclusion of patient with clinical symptoms of COVID-19 infection (fever, signs of acute respiratory infection, loss of taste or smell) during hospitalization due to acute stroke*
*Randomization criteria*	
1. AHI > 20/h	

*AHI* apnoea-hypopnoea index, *ASV* adaptive servo-ventilation, *ECASS* European Cooperative Acute Stroke Study, *MRI* magnetic resonance imaging, *NYHA* New York Heart Association

*Notes: COVID-19 testing algorithms of each centre apply and each centre must adhere to their country’s official standards and government guidelines

#### First step

The study physician selects patients eligible for respiratory polygraphy depending on patients’ age (18–85 years), stroke location (supratentorial), stroke size on diagnostic imaging and state of consciousness and respiratory independence (no coma/intubation). After this first screening step and depending on centres’ standard operating procedures, a respiratory polygraphy is prescribed within clinical routine or as part of the trial in the first night after stroke. Accordingly, a study physician collects the patient’s or his/her next-of-kin’s/legal representative’s informed consent before or after the respiratory assessment.

#### Second step

Based on the result of the respiratory polygraphy, the lesion diameter confirmed on the MRI at day 1, and after the study physician has checked the remaining exclusion criteria listed in Table 1, eligible patients with significant SDB (AHI > 20/h) are randomized to ASV treatment (SDB ASV+) versus no ventilation treatment (SDB ASV−) applied between the 2nd and 89th night following stroke. Eligible patients with an AHI < 5/h can be included into the control cohort without SDB (noSDB group). Figure 1 gives an overview on the study design.

**Fig. 1 Fig1:**
[figure not shown]
Study flow chart. Ischaemic stroke patients admitted within 24 h of symptom onset undergo respiratory polygraphy on night 1. Patients with AHI > 20/h are randomized to ASV versus no ASV treatment. Patients with AHI < 5/h are followed in parallel. New cerebro-cardiovascular events or death are assessed after 1 year by telephone interview. Abbreviations: AHI, apnoea-hypopnoea index; SDB, sleep-disordered breathing; ASV, adaptive servo-ventilation

Every centre uses the same screening log. To identify the main reasons why patients are not eligible and to take action in case of potential screening and recruitment difficulties, each centre sends its anonymized screening log to the coordinating study team in Bern on a regular basis. Based on the screening experience in Bern before the trial became multicentre, eligibility criteria were adapted to increase the number of potentially eligible patients and generalizability of results. The main adaptations included a reduction of inclusion AHI from 30/h to 20/h, extension of upper age limit from 80 to 85 and elimination of NIHSS > 4 as an inclusion criterion. These modifications are trackable on clinicaltrials.gov.

Beside bi-annual investigator meetings, trial progression is also evaluated by the Swiss National Science Foundation (SNSF), the main financial supporter of the trial, based on bi-annual progress reports provided by the coordination centre of Bern.

To ensure retention and follow-up of each patient, follow-up visits are planned together with the patients and where possible combined with clinical routine visits. A study nurse reminds patients of their onsite visit by a phone call or letter and organizes the transport from their home or rehabilitation unit to the hospital if necessary. We also provide patients with our contact information (e-mail, phone) and encourage them to call in case of any also medical question.

### Sleep assessment

Respiratory polygraphy is performed during the first night following stroke onset using a Nox-T3 respiratory polygraph (Nox Medical, Inc., Reykjavik, Iceland), according to standard procedures provided by the manufacturer. This device allows the recording of nasal pressure, snoring, rib cage and abdominal movement, pulse oximetry, activity and body position.

Respiratory polygraphies are analysed by a certified sleep physician immediately on the next day (visit 1, study day 1) to allow inclusion of eligible participants (Fig. 1). Respiratory polygraphies are repeated at visit 6 (day 90 ± 7) to examine the evolution of SDB following a two-week washout period involving a temporary discontinuation of ASV therapy.

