
##### Assessment of ASV treatment compliance

Compliance to ASV treatment is checked daily during the initiation of ASV treatment using the devices internal recordings. Thereafter, verification of compliance takes place at clinical controls at visits 2, 4, 5 and 6. Sufficient compliance is defined as a cumulative ASV use in ≥ 70% of all nights and ≥ 4 h per night in the first 3 months after stroke. All patients who started ASV treatment/training will be analysed as ASV patients (intention to treat; ITT). For secondary analyses, patients with SDB are stratified according to their compliance: compliant patients (per protocol, PP) will be compared to non-compliant participants and to participants who did not receive ASV-treatment.

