### Statistical analysis

Descriptive summary statistics for efficacy and safety variables will be presented for the entire population and by study arm (no SDB patients, and SDB patients randomized to the ASV+ and ASV- arms). Inferential statistical methods will be used to highlight interesting aspects of the data and primarily for the comparison of outcome variables in the two randomized arms. In addition, comparisons of selected outcomes will be carried out between the two cohorts. The significance level of all statistical tests will be 5% and no control for multiplicity will be applied. Corresponding 95% confidence intervals will be presented as appropriate.

Two main analysis populations will be used:
*Full Analysis Set (FAS)*: this population will include all enrolled patients. In line with the intent-to-treat principle, randomized patients will be analysed according to the treatment group assigned at randomization. The FAS will be the main analysis population for efficacy and safety variables. In particular, it will be the primary population for the comparative analysis of the two randomized treatment groups.*Per-protocol (PP) population*: it will include randomized patients fulfilling all selection criteria and sufficiently compliant with the protocol. The list of criteria, leading to exclusion from the PP analysis, which, among other criteria, will consider the compliance with ASV procedures, will be finalized before database closure for the primary analysis.

The comparative analysis of infarct volume data will be performed using an analysis of covariance model with adjustments at least for the stratification variables used at randomization. In case of violation of the statistical validity conditions for the model, a suitable non-parametric alternative model will be employed, such as the Van Elteren test.

Between-arm comparisons of continuous variables will be performed using the same methodology as for the primary variable, whereas models may include additional explanatory variables, such as the baseline value of specific outcome variables assessed at study end. Logistic regression will be used for comparisons based on binary variables.

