## Discussion

eSATIS trial is the first trial to assess the impact of immediate treatment of significant SDB (AHI > 20/h) in acute ischaemic stroke patients with non-invasive ASV on infarct progression in a prospective interventional randomized controlled design. The trial will give information on the feasibility and efficacy of ASV treatment in patients with stroke and SDB and allow assessing the impact of SDB on stroke outcome. Diagnosing and treating SDB during the acute phase of stroke is not yet current medical practice. Evidence in favour of ASV treatment from a randomized multicentre trial may lead to a change in stroke care and to improved outcomes.

Limitations of this trial include the following: (1) The compliance to ASV is expected to be around 50%. This will have an impact on the interpretation of results. (2) The treatment is open label, which may result in a bias affecting the assessment of secondary clinical outcomes. However, sham ventilation may cause even greater distress in patients than effective ASV treatment without beneficial effects on sleep quality and improvement of daytime sleepiness and is ethically questionable. (3) It is unknown whether the sample size of 134 randomized patients will be sufficient to detect the real treatment effect, since no data on the impact of ASV treatment on the evolution of the lesion volume are available so far.

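### Applied as printed, the compliance rule counts the mandated two-week ASV washout as non-use, so it asks for about 84% of permitted nights at a day-90 visit

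*Protocol article*

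**What the plan says.** Four places in the protocol article bear on this.

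- **Assessment of ASV treatment compliance** sets the threshold: "cumulative ASV use in ≥ 70% of all nights and ≥ 4 h per night in the first 3 months after stroke". No nights are exempted. The same section puts the rule to use in secondary analyses, where "compliant patients (per protocol, PP) will be compared to non-compliant participants" and also to patients who had no ASV.
- **Sleep assessment** schedules a repeat polygraphy at visit 6 (day 90 ± 7), "following a two-week washout period involving a temporary discontinuation of ASV therapy".
- **Second step** (under screening and recruitment) gives the treatment period: ASV or no ASV is "applied between the 2nd and 89th night following stroke".
- **Statistical analysis** leaves the per-protocol exclusion list open. The list "will consider the compliance with ASV procedures, will be finalized before database closure for the primary analysis".

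**The concern.** A patient who follows the protocol exactly must stop ASV for two weeks inside the period over which compliance is scored. Those nights stay in the denominator, so the printed 70% is not 70% of what the patient was allowed to do. Some patients who used the device on more than 70% of the nights open to them would be sorted into the non-compliant group because they obeyed an instruction.

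What is at stake is how cleanly the compliant and non-compliant groups are separated in a secondary, non-randomized comparison. The Discussion expects compliance of only about 50% and says this will affect interpretation, so readers are likely to look at that comparison.

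**Working it through.** **Inputs from the article.** Threshold: 70% of nights. Treatment period: nights 2 to 89. Washout: two weeks, taken as 14 nights ending the night before visit 6. Visit 6: day 83 to day 97. The article prints no share of permitted nights, so there is no stated figure to reproduce. A permitted night here means a night in the scoring period outside the washout. A night counts as used only if the 4-hour condition is met.

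**Where the washout falls.** If it began only after night 89, the polygraphy would come near day 89 + 14 = 103, beyond the last allowed day, 97. So at least part of the washout lies inside nights 2 to 89.

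**Visit 6 on day 90.**
- Nights in the period: 89 − 2 + 1 = 88
- Nights required: 0.70 × 88 = 61.6, so 62
- Nights permitted: 88 − 14 = 74
- Effective bar: 62/74 = 83.8%
- Highest attainable score: 74/88 = 84.1%

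**If only permitted nights were counted.** 0.70 × 74 = 51.8, so 52 nights. The patients whose class turns on the reading are those with 52 to 61 nights: 52/74 = 70.3% up to 61/74 = 82.4%.

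**Other visit days.** The article does not say whether counting stops at night 89 or at the visit, so both are shown. Counting to night 89 for the early visits assumes that ASV resumes after the polygraphy.

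| Counting convention | Visit day | Required | Permitted | Bar |
|---|---|---|---|---|
| To night 89 | 83 to 90 | 62 | 74 | 83.8% |
| To night 89 | 97 | 62 | 81 | 76.5% |
| To the visit | 83 | 57 | 67 | 85.1% |
| To the visit | 85 | 59 | 69 | 85.5% |
| To the visit | 90 | 62 | 74 | 83.8% |
| To the visit | 97 | 67 | 81 | 82.7% |

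For day 97 counted to night 89, only nights 83 to 89 (7 nights) of the washout fall inside the period, so 88 − 7 = 81 are permitted. For day 85 counted to the visit, nights 2 to 84 are 83 nights, 0.70 × 83 = 58.1 gives 59, and 83 − 14 = 69. These two rows are the extremes over all visit days. Under either convention the bar is above 70%.

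**The case against.** The strongest reply is that this is a matter of detail. The article condenses a longer protocol and refers to an analysis plan, and the per-protocol list is expressly unfinished. An analyst could sensibly take all nights to mean nights on which ASV was due. A second reply is that the literal rule may be intended as a minimum exposure over three months. It is attainable, since a perfect user scores 84%, and on that view a patient with 52 to 61 nights (59% to 69% of 88) is rightly below it.

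Both replies carry some weight, and they keep the point minor. They do not remove it. The article does not leave the rule unstated: it prints a numeric definition with its period, and a washout elsewhere in the text takes nights out of that period. Neither the prescribed-nights reading nor the minimum-exposure reading is written down, and the open per-protocol list does not say that the denominator will be adjusted.

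A reader might infer more than the document supports:

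- **That the night 2 to 89 period contradicts the washout.** It can be read as the outer limits of treatment with the washout as a break inside them.
- **That the bar shifts materially with the visit date.** Take two patients who each use ASV on about 80% of permitted nights. Counting to night 89, the day-90 patient fails (59 of 74, against 62) and the day-97 patient passes (65 of 81, against 62). Counting to the visit, the second also fails (65 against 67). The example depends on a counting convention that the article does not fix.
- **That compliance will fall below the expected 50% or so.** The article does not say which denominator that expectation uses.

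**Conclusion.** The point holds for the rule as printed. At a day-90 visit the effective bar is about 84% of permitted nights instead of 70%, and patients with 52 to 61 of 74 permitted nights are classed as non-compliant. Over the allowed visit days and both counting conventions the bar runs from 76.5% to 85.5%. This rests on a 14-night washout ending at visit 6 and on literal application of the rule.

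It is a minor point. Only the secondary compliance-stratified and per-protocol comparison is touched. A reader might suppose that the main result or the power is at risk, but the primary analysis keeps randomized patients in their assigned groups whatever their device use, and the sample size calculation contains no compliance term. The number of patients who would change class is unknown, because the article gives no distribution of nightly use. For the same reason, neither the size nor the direction of any effect on the secondary comparison can be derived.

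**What to change.** When the per-protocol criteria are finalized, define the compliance denominator as the nights on which ASV was prescribed, excluding the mandated washout, and state where the washout sits within nights 2 to 89. The 70% threshold then means at least 52 of 74 nights at a day-90 visit and 57 of 81 at day 97 (0.70 × 81 = 56.7). Merely adding a sentence that washout nights count would make the policy explicit but leave the sorting as it is.

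The cost is wording only, since the devices already record use. The downside is lower total exposure among patients called compliant: 52 nights is 52/88 = 59% of the treatment period, against 62 nights under the literal rule. The change should be made before database closure, so that the choice of who counts as compliant is not made after the results are known.
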